### Eligibility criteria {10}

All parents of infants born at less than 32 weeks of GA and admitted to the participating units will be approached by one of the research team members within the first week of life (as full enteral feeding is usually reached at a minimum of 7 days of life). Recruitment will take place between June 2019 and December 2021. After obtaining written consent for participating in the trial, the patient’s medical record number (MRN) will be immediately registered on a secure web-based platform and demographic data will be recorded.

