#### Inclusion criteria

Patients eligible for the trial must comply with all of the following at randomization:
Gestational age at birth ≤32 weeksEnteral feeding of at least 80 ml/kg/day50% donor or maternal milk-based enteral feedingParenteral/legal guardian consent

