#### Intervention description {11a}

After reaching 80 ml/kg/day of enteral feeding, patients will be randomized to receive SF (Bebilon HMF, Nutricia) or TF (protein: Bebilon Suplement Bialka, Nutricia; lipids: Calogen, Nutricia; carbohydrates: Polycal, Nutricia) (Fig. 1). The content of macro- and micronutrients of each product is given in Table 1.

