The desired macronutrient concentration in breast milk will be 4.4 g/100 ml of fat, 3 g/100 ml of protein, and 8.8 g/100 ml of carbohydrate in order to meet the European Society for Paediatric Gastroenterology, Hepatology, and Nutrition (ESPGHAN) guidelines (6.6 g/kg/day of fat, 4.5 g/kg/day of protein, and 13.2 g/kg/day of carbohydrate) assuming an intake of 150 ml/kg/day.

Target fortification (TF) will be done in 3 steps:
Determination of macronutrient concentration in own OMM/HDMSF: human milk fortifier, HMF NutriciaTF: adding fat, protein, and/or carbohydrate to achieve target levels of macronutrients

In cases where a macronutrient component after SF will exceed the target value, only the other deficient macronutrient components will be adjusted.

To enhance feeding tolerance at the start of the intervention, TF will be gradually introduced in a stepwise manner over a 3-day period (maximum target dosage of added fat, protein, and carbohydrate will be as follows: at day 1, 0.3 g; day 2, 0.6 g; and day 3, 0.9 g per 100 ml breast milk), as suggested by Rochow et al. [12]. On day 4, the full amount of target fortification for each macronutrient will be prescribed; this day will be marked the starting point of the intervention period. Patients will be fed every 3 h via a gastric tube by registered nurses. Starting from 33 weeks of post-conceptional age (PCA), non-nutritive sucking stimulation will be initiated by occupational therapists. At approximately 34 weeks of PCA, infants will be transitioned to bottle feeding. When breastfeeding is established, patients will receive TF as one or two bottle feeds.

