#### Secondary outcomes

Growth (weight, length, head circumference) will be assessed at discharge and at 4 months of corrected age.Body composition (percentage of body fat, fat mass, fat-free mass) will be measured at discharge and at 4 months corrected age by air plethysmography (PeaPod).^1^Neurodevelopmental outcome:
12 months corrected age: BSID-III (Bayley Scale of Development Third Edition); the following stratification of index composite scores will be used in our study:< 70 (> 2 SD below the mean)—severe impairment70–84 (> 1 SD below the mean)—mild impairment≥ 85—normal development3.5 years of corrected age: BSID and WPSSI-IV (Wechsler Preschool and Primary Scale of Intelligence, Fourth Edition IV).Behavioural problems: parental assessment by CBCL (Child Behaviour Check List) at 3.5 years corrected age.Feeding tolerance under whole period of fortification.Morbidity: incidence of necrotizing enterocolitis (NEC), retinopathy of prematurity (ROP) and bronchopulmonary dysplasia (BPD), intraventricular haemorrhage (IVH), periventricular leukomalacia (PVL), sepsis, and pneumonia. Definitions provided below.

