##### Definitions

Feeding tolerance: defined as haemorrhagic residuals or vomiting bile until pathological causes are ruled out (intestinal obstruction or ileus) [17]. Gastric residuals and abdominal girth will not be checked routinely. Isolated green or yellow residuals will be considered unimportant.NEC (necrotizing enterocolitis): stage II or III. Stage II requires clinical manifestations of distended abdomen and radiological verification (intramural and/or portal gas). Stage III requires findings like in stage II and more severe clinical symptoms (shock, need for respirator). In surgery verified cases, no radiological verification is needed [18].ROP (retinopathy of prematurity): stages I to V, diagnosed by an ophthalmologist according to international criteria [19].BPD (bronchopulmonary dysplasia): need for oxygen, continuous positive airway pressure (CPAP), or mechanical ventilation at 36 + 0 weeks gestational age [20].IVH (intraventricular haemorrhage) [21].PVL [21].Early- and late-onset sepsis defined as a positive blood or cerebral fluid culture at less or more than 72 h of age, respectively [22].

Feeding tolerance has been chosen as an efficacy and harm outcome in order to evaluate whether TEN may impact milk absorption in the intervention group. Exclusive breastfeeding decreases the risk of NEC; however, the impact of TEN on the risk of developing NEC has not yet been studied. Blood culture confirmed early-onset sepsis (EOS) is a known risk factor for delayed implementation of EN and can impact the risk of late-onset sepsis (LOS). Diagnosis of EOS and LOS can be associated with intermitted withdrawal of enteral nutrition, BPD, IVH, and PVL which are markers of neonatal morbidity; hence, we decided to include them in our analysis.

Time schedule of enrolment, interventions (including any run-ins and washouts), assessments, and visits for participants is presented in Table 2.

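### Early-onset sepsis, and IVH or PVL already present, are counted as morbidity outcomes although they ordinarily precede randomisation

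*Protocol article*

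**What the plan says.** All references are to the protocol article.

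- **Outcomes {12}, Secondary outcomes** lists the morbidities compared between arms by incidence. They include "intraventricular haemorrhage (IVH), periventricular leukomalacia (PVL), sepsis, and pneumonia", and the reader is referred to the definitions that follow.
- **Outcomes {12}, Definitions** splits sepsis at 72 h: "Early- and late-onset sepsis defined as a positive blood or cerebral fluid culture at less or more than 72 h of age, respectively". IVH and PVL receive a name and a citation only: "IVH (intraventricular haemorrhage) [21].PVL [21". No grade, onset window or rule for lesions already present is given.
- The same section explains why early-onset sepsis is recorded: "Blood culture confirmed early-onset sepsis (EOS) is a known risk factor for delayed implementation of EN". It adds that early-onset sepsis can influence late-onset sepsis, and then places these diagnoses in the analysis without separating baseline factors from outcomes.
- **Intervention description {11a}** fixes when allocation takes effect: "After reaching 80 ml/kg/day of enteral feeding, patients will be randomized to receive SF". **Inclusion criteria** makes the feeding volume a condition to be met at that moment: "Patients eligible for the trial must comply with all of the following at randomization".
- **Eligibility criteria {10}** gives the only timing of feeding progress: "as full enteral feeding is usually reached at a minimum of 7 days of life".
- **Exclusion criteria** lists sepsis, without an onset time and without saying whether a resolved episode counts.

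**The concern.** A morbidity outcome in a randomised comparison should be able to respond to the allocated treatment. An event that has already happened at randomisation cannot. It is a baseline characteristic, and the article's own rationale gives early-onset sepsis that role by calling it a risk factor for what comes later.

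If such events are counted, they add the same expected number of cases to both arms. That pulls the risk ratio towards 1 and lowers power, so a real benefit or harm in late-onset sepsis, IVH or PVL is harder to see. The article plans no interim analysis and no data monitoring committee, so the final comparison is where such a difference would show.

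Elsewhere the article does apply an onset rule: under Adverse event reporting and harms {22}, NEC and gastrointestinal obstruction count as serious adverse events only after the study nutrition has begun. The secondary outcomes have no matching rule.

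**Working it through.** **Step 1. Does early-onset sepsis precede randomisation?**

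Inputs: threshold for randomisation 80 ml/kg/day (Intervention description {11a}); full feeds usually at day 7 at the earliest (Eligibility criteria {10}); volume at full feeding 150 ml/kg/day (the target concentrations are set "assuming an intake of 150 ml/kg/day"), or 160–170 ml/kg/day, the limit on daily intake in section {11d}. The article gives no age for 80 ml/kg/day, so I assume a linear advance from birth.

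Age at 80 ml/kg/day = (80 / full volume) × 7 days × 24 h

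- 150 ml/kg/day: 80/150 × 168 h = 89.6 h (3.7 days)
- 160 ml/kg/day: 80/160 × 168 h = 84.0 h (3.5 days)
- 170 ml/kg/day: 80/170 × 168 h = 79.1 h (3.3 days)

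All exceed 72 h, and they describe the fastest usual course. To reach the threshold by 72 h on a straight line, the day-7 volume would have to be 80 × 7/3 = 187 ml/kg/day, above every figure in the article. Early-onset sepsis therefore ordinarily comes before randomisation.

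**Step 2. What follows for sepsis?**

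Let e be the share of randomised infants with the event before randomisation.

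- If the sepsis exclusion covers early-onset cases, e = 0. The sepsis comparison is not diluted, but the early-onset outcome cannot occur.
- If it does not, e > 0. A separate late-onset comparison is still undiluted; a single pooled sepsis comparison is diluted.

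**Step 3. What follows for IVH and PVL?**

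No exclusion applies and no onset rule is given, so lesions already present at randomisation are counted. The article gives neither rates nor onset times, so their share cannot be computed.

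**Step 4. How large could dilution be?**

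The article states no figure for the morbidity outcomes, so there is none to reproduce. I use its recruitment target of 200, that is 100 per arm. Every rate below is an assumption: risk after randomisation 20% (control) vs 10% (targeted), and e equal in both arms. Two ways of combining events bracket the result:

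- no infant has both events: risk = e + p
- events independent, overlap allowed: risk = 1 − (1 − e)(1 − p)

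Power is by exact enumeration of the two-sided chi-square test at the 5% level.

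| e | Combination | Control vs targeted | RR | Power |
|---|---|---|---|---|
| 0 | – | 20.0% vs 10.0% | 0.50 | 0.518 |
| 5% | no overlap | 25.0% vs 15.0% | 0.60 | 0.431 |
| 5% | overlap | 24.0% vs 14.5% | 0.60 | 0.406 |
| 10% | no overlap | 30.0% vs 20.0% | 0.67 | 0.371 |
| 10% | overlap | 28.0% vs 19.0% | 0.68 | 0.323 |

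For example, with overlap and e = 10%: 1 − 0.9 × 0.8 = 0.28, 1 − 0.9 × 0.9 = 0.19, and RR = 0.19/0.28 = 0.68. If 30% of infants already had the event (overlap allowed), the risks would be 44% vs 37%, the RR 0.84 and power 0.176.

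**The case against.** The strongest reply is that dilution of sepsis is not established. Sepsis is an exclusion criterion, while sepsis during treatment is dealt with separately as a reason for discontinuation ({11b}). The natural reading is that infants with early-onset sepsis are never randomised. Early- and late-onset sepsis are also defined apart, and nothing says that they will be pooled. This stands. A reader might infer that early-onset cases will certainly dilute the sepsis comparison; the article does not support that. Dilution needs both that such infants are randomised and that the two types are combined. What remains is that the outcome list names a single item, sepsis, and that on either reading the exclusion and the definition do not fit together.

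For IVH and PVL, onset times and rates are not given, the definitions rest on a cited source, and the assessment schedule is not reproduced in the text available. Lesions arising after randomisation are valid outcomes. So the point is confined to lesions already present, and its size is unknown.

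The timing rests on a linear advance, and the day-7 figure refers to full feeds, not to 80 ml/kg/day. Concealment mechanism {16b} also reads as if allocation follows consent in the first week. Neither rescues early-onset sepsis as an outcome: even with earlier allocation, study fortification begins only after the feeding threshold.

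It is also fair that the events named for adverse-event reporting in {22} are tied to the introduction of the study nutrition, so that reporting is not affected. Finally, counting rules for secondary outcomes are often left to an analysis plan. Here, though, the article itself writes the pre-randomisation event into the outcome definition.

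**Conclusion.** The point holds in a limited form. As written, the morbidity outcomes include early-onset sepsis, which ordinarily precedes randomisation and cannot be changed by fortification, and they place no onset limit on IVH or PVL. For sepsis the result is either an outcome that cannot occur or, if early-onset cases are randomised and pooled, a risk ratio drawn towards 1. For IVH and PVL, any pre-existing lesions dilute the comparison by an amount that the article does not allow to be computed.

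Under the assumed rates, power falls from 52% to 41–43% with 5% pre-existing events and to 32–37% with 10%. These figures show the mechanism and do not estimate the loss in this trial, which is not sized for these comparisons: even undiluted, power is only about one half. A reader might also infer bias in favour of one arm, or a threat to the main result. Neither follows: pre-randomisation events are balanced in expectation, and the primary outcome is weight gain velocity.

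**What to change.** In Secondary outcomes and Definitions under Outcomes {12}:

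1. Count as outcomes only late-onset sepsis, and new or worsened IVH and PVL, with onset after randomisation. The onset condition is needed for late-onset sepsis too, because an episode can begin after 72 h and still precede randomisation.
2. Report early-onset sepsis, and IVH and PVL present at randomisation, as baseline characteristics by arm.
3. Reconcile the sepsis entry under Exclusion criteria with the sepsis outcome, so that it is clear whether infants with early-onset sepsis can be in the randomised population.

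The cost is a sentence or two of text and no extra infants. Onset dates must be recorded; the time of a positive culture is already needed to apply the 72 h cut-off, but IVH and PVL also need a record of status at randomisation. Slightly fewer events will be counted, but those dropped carry no information about the intervention.

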**Table 2 Tab2:**
[figure not shown]
Enrolment, interventions, and assessments schedule

*DOL* day of life, *T1* enteral nutrition 80 ml/kg/day of own mother’s milk or human donor milk, *T2* 4 weeks of life, *T3* 8 weeks of life, *T4* 12 weeks of life/discharge, *T5* 4 months of corrected age, *CBC* complete blood count, *BUN* blood urea nitrogen

### Participant timeline {13}

It is provided in Table 2.

### Sample size {14}

The sample size required to compare two means in two-sided equality test was estimated based on results from a prior double blind, randomized clinical trial, investigating the effect of TG vs SF of breast milk on the changes of anthropometric parameters and body composition in preterm children [23, 24]. It was determined that a mean difference of weight gain 1.9 g/kg/day between groups would be clinically important and feasible during intervention.

The following assumptions were made for the calculation: type I error (α) 5%, power 80%, equal sample sizes in both groups, the mean weight gain in the standard fortification group 19.3 g/kg/day, and the mean weight gain in the target fortification group 21.2 g/kg/day. To account for the higher uncertainty in measured weight gain due to differences between the studied and the quoted trial population, standard deviation value taken from the prior trial was increased by 50% to 3.75.

An estimated minimum size of each group is 68. Accounting for a presumed 20% attrition rate, due to potential dropouts, deviations from the protocol, and loss to follow-up, a minimum sample size required was estimated at 156 infants or 78 infants per treatment arm.

However, in order to detect a difference of 5 points in cognitive score of Bayley-III (secondary outcome) at 12 months of age (mean of 100 points, standard deviation (SD) 12) between the study groups with a power of 80% and α = 0.05, we have decided to increase the sample to 91 infants in each study group.

In summary, allowing for 10% of loss to follow-up, the target number of 200 premature infants will be recruited.

### Recruitment {15}

The study will continue until the minimum of 200 valid observations are collected in every arm. As part of the antenatal consult, women with threatened preterm labour will be scheduled a short meeting with a member of the recruitment team. During this appointment, they will be offered participation in the trial. In order to increase participant enrolment, a second patient screen will be carried out by medical staff during admission to the NICU. The enrolment period will extend over 18 months. Recruitment rates will be monitored monthly. In return, women will be offered additional breastfeeding support by a certified lactation consultant (lactation stimulation programme, Fig. 2).

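### The recruitment section runs the trial to at least 200 valid observations per arm (400 or more in total), while the sample size section derives a target of 200 infants over both arms

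*Protocol article*

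**What the plan says.** Section Sample size {14} first sizes the trial for weight gain. It then enlarges it "in order to detect a difference of 5 points in cognitive score of Bayley-III (secondary outcome) at 12 months of age", assuming a "mean of 100 points, standard deviation (SD) 12", with 80% power and α = 0.05: "we have decided to increase the sample to 91 infants in each study group". It closes with the recruitment figure: "allowing for 10% of loss to follow-up, the target number of 200 premature infants will be recruited".

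Section Recruitment {15} opens with a different rule: "The study will continue until the minimum of 200 valid observations are collected in every arm". Section Trial design {8} defines two parallel arms at 1:1, so this rule asks for at least 400.

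The length of enrolment also varies. Recruitment {15} says: "The enrolment period will extend over 18 months". Eligibility criteria {10} says: "Recruitment will take place between June 2019 and December 2021". Trial status gives a start on 1 June 2019 and an approximate end on 31 December 2022, without making clear whether recruitment or the whole study ends then.

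**The concern.** The sentence in Recruitment {15} is the only one that says when the trial stops enrolling, and its number does not come from the sample size calculation. Someone following the sample size section would stop at 200 infants. Someone following the recruitment section would carry on to more than twice that number. Once the trial has ended, no one could tell from the protocol whether stopping at 200, 300 or 400 was according to plan.

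The counting unit adds to the difficulty. The number of infants randomised is known at every moment and does not depend on what happens afterwards. The number of valid observations depends on later events. If it means complete records, it depends on withdrawal and on discontinuation of the intervention. If it includes the Bayley-III score at 12 months, it is not known until long after the last infant has been enrolled. Such a count cannot readily govern the close of recruitment.

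**Working it through.** **1. Reproduce the plan's own figure.** Inputs from Sample size {14}: difference 5 points, SD 12, power 80%, α = 0.05 (taken as two-sided).

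n per arm = 2 × (1.96 + 0.8416)² × 12² / 5² = 2 × 7.849 × 5.76 = 90.4, rounded up to **91**. This matches the stated 91 (a t-based calculation gives 92).

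- Evaluable infants in both arms: 2 × 91 = 182.
- Recruited, allowing for 10% loss: 182/0.9 = 202.2, rounded up to 203. The cruder 182 × 1.1 = 200.2 also points to about 200.

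So the 200 in Sample size {14} is a total over both arms.

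**2. The rule in Recruitment {15}.**

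- Valid observations: 2 × 200 = 400.
- Infants randomised at 10% loss: 400/0.9 = 444.4, about 445.
- At 20% loss: 400/0.8 = 500.

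**3. Size of the gap.**

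| Basis | Sample size {14} | Recruitment {15} | Ratio |
|---|---|---|---|
| Figures as printed, both arms | 200 | 400 | 2.0 |
| Evaluable infants | 182 | 400 | 2.2 |
| Randomised, 10% loss | 200 | about 445 | 2.2 |

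The first row compares infants recruited with valid observations. The like-for-like ratio is about 2.2, a difference of about 245 infants.

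**4. Power under each reading** (normal approximation, two-sided 5%; weight gain uses the plan's difference of 1.9 and SD of 3.75 g/kg/day).

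| Evaluable per arm | Weight gain | Bayley-III |
|---|---|---|
| 91 | 93% | 80% |
| 200 | 99.9% | 98.6% |

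Nothing in the document asks for the power in the second row.

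**5. Could the literal rule be met?** Study setting {9} gives approximately 100 deliveries per year at or below 32 weeks. I assume that this is per site, at three sites, with one infant per delivery.

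- 18 months: 3 × 100 × 1.5 = 450.
- June 2019 to December 2021, 31 months: 300 × 31/12 = 775.

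| Number to randomise | Share of 450 | Share of 775 |
|---|---|---|
| 200 | 44% | 26% |
| 445 (10% loss) | 99% | 57% |
| 500 (20% loss) | 111% | 65% |

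If the 100 covered all sites together, the pools would be 150 and about 258. Then even 200 infants could not be found in 18 months, which makes that reading unlikely.

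**6. Enrolment period.** Eighteen months from 1 June 2019 end on 30 November 2020. Eligibility criteria {10} runs 13 months longer.

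**The case against.** The strongest reply is that the words about every arm are a drafting slip. The derivation leads to 200 as a total, the same number reappears in the next section, and no calculation supports 200 per arm. I think this is the likely explanation. The document does not say so, however, and the slip sits in the sentence that governs when enrolment ends. Nor does either reading leave the primary comparison short of infants: power for weight gain is about 93% at 91 per arm. The defect is an inconsistency in the trial's size and end, not a loss of power for the primary outcome.

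It can also be said that a journal article need not define a valid observation. I accept that, and the missing definition is not the point here. The point is that the rule as printed counts something that accrues after randomisation, whereas the sample size section sets a number to recruit.

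A reader might infer three stronger things that the document does not support:

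- *That the literal target cannot be met.* It exceeds the assumed pool only with 20% loss and the 18-month period. At 10% loss it is 99% of that pool, and over 31 months it is 57% to 65%. The exclusions, the language requirement and refusals make the higher shares unrealistic, but the pool is itself an assumption: the protocol counts deliveries, not infants, and only approximately.
- *That the team could choose between 200 and 400 in the light of emerging results.* Interim analyses {21b} plans no interim analysis, and Who will be blinded {17a} blinds treating physicians, bedside nurses, the psychologist and data analysts. The statistical team holds the randomisation list, so the possibility is not nil, but nothing in the text points to it.
- *That December 2021 is the correct end of enrolment.* Three statements differ or are unclear, and none is marked as governing.

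**Conclusion.** The contradiction stands in the current text, and no other section resolves it. Sample size {14} supports about 200 infants in total. Recruitment {15} requires at least 400 valid observations, or about 445 infants randomised at 10% loss. The ratio is 2.0 on the printed figures and 2.2 like for like. This rests on reading an observation as one infant; counting repeated measurements would give no usable rule. The sentence in Recruitment {15} is wrong as written and needs correction, because it sets the end of the trial and does so in a unit known only after randomisation. The feasibility shares depend on the assumed pool and show only that the literal target is demanding. The discrepancy in enrolment dates is real but separate.

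**What to change.** Replace the sentence in Recruitment {15} with a rule that agrees with Sample size {14} and refers to infants randomised, for example: *Recruitment stops when 200 infants in total (about 100 per arm) have been randomised, regardless of later withdrawals or data completeness.*

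State what that number delivers. At 10% loss, 100 per arm leaves 90, just under the 91 derived, and Bayley-III power is still about 80%. Holding strictly to 91 would need 91/0.9 = 101.1, so 102 per arm or 204 in total. The section on participant retention {18b} allows for loss of up to 20% a year. At 20% loss, 100 per arm leaves 80, and Bayley-III power falls to about 75%: 5/(12 × √(2/80)) = 2.635, less 1.96 = 0.675. The sponsor should say which loss rate the target assumes.

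Separately, give one enrolment period in Recruitment {15} and Eligibility criteria {10}, and label the 31 December 2022 date in Trial status as end of recruitment or end of study. The sponsor has to supply the correct dates.

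If 200 in total is the intended figure, the cost is an amendment of wording with no extra infants; going to 204 would add four. If 200 per arm was really intended, the sample size section needs a justification that it does not now contain.
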